Treatment is delivered in the community as much as possible. The basic philosophy of the CB&BT team involves supplying 'system-oriented tailored care': the optimal combination and intensity of interventions is established for each client system. These can vary during the course of the treatment. Treatment continuity is a goal; treatment is delivered as much as possible by the same two therapists. The therapists come from different disciplines: doctors (residents), psychiatrists, psychologists and psychiatric nurses. The core team consists of experienced therapists. The team is supplemented by a group of residents that changes every six months. The primary focus of the treatment is to help clients regain a sense of mastery over their lives again. However, compulsory admissions also take place when necessary if clients are unfit to make their own decisions and their behaviour is dangerous.

Therapists can ask for consultation about difficult cases any moment. A consulting psychiatrist is always available, and daily case meetings are open to any therapist who faces a problem or feels a case is not progressing. This means there is no principal difference in the quality and availability of services between TAU and Experimental Intervention.

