#### Primary analysis: EXP versus TAU

In the primary analysis, outcomes of the two treatment conditions will be compared using repeated measures analysis (GLM), with the number of sessions as a covariate. In this analysis, each follow-up measurement will be compared separately to the baseline measurement. Since in this design patients are nested within therapists, these nested data will also be examined in a multilevel analysis, controlling for therapist variation. The number of sessions will be included as a covariate.

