### Feedback and client and therapist variation

If some therapists are generally more effective than others, then the outcomes of clients seen by the same therapists will be correlated. Three multilevel models will be constructed to examine therapist and client effects as well as the effects of feedback on posttreatment functioning, similar to the analysis by Anker et al. [31]. In Model 1, the presence of therapist and client effects will be tested by controlling for pretreatment functioning at Level 1 and evaluating the residual intraclass correlations. To determine the variance due to therapist and client, the residual intraclass (controlling for pretreatment ratings) correlation will be calculated. In Model 2, the effect of feedback will be estimated, and in Model 3 a random slope for feedback will be added to examine if the effect of feedback varies across therapists.

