### Patients in crisis

Another factor is that clients are referred to the team in crisis situations. This means it is a highly vulnerable group of people in desperate circumstances who, as a result of avoidance or resistance, have passed through every safety net and who often function poorly. For those patients, providing reflective feedback focusing on the patient's own situation and the relationship with the mental health services will probably be quite challenging. Otherwise, the service works in shifts, which means that changes in staffing are sometimes inevitable and the standard approach is to work with co-therapy pairings (to safeguard both quality and continuity). So the therapeutic relationship is split up between several people, which might complicate the feedback about the alliance. Finally, the therapists are a mixed group of highly experienced permanent staff (6 psychiatrists, 10 social psychiatric nurses, two psychologists and a system therapist) and relatively experienced doctors (28 years on average, some of whom are being trained as psychiatrists) to work in the team temporarily for an average of six months; this means that specific expertise can vary considerably from therapist to therapist.

Another limitation of the study is that the feedback instrument does not provide information about the influences of social support, changes in the primary domains of a persons life and historical developments concerning the family of origin, which can be of importance for understanding the broader context of the change process [64].

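### The multilevel models treat each patient as nested in one therapist, but care is given by co-therapy pairs, so the therapist variance and the random slope for feedback may be misestimated by an amount the protocol does not allow one to fix

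*Protocol article*

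**What the plan says.** All references are to the protocol article.

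**What the analysis assumes.** The section *Primary analysis: EXP versus TAU* gives the data structure as the reason for a multilevel model that controls for therapists: "Since in this design patients are nested within therapists, these nested data will also be examined in a multilevel analysis". The secondary analyses under *Feedback and client and therapist variation* build on it. For Model 1: "To determine the variance due to therapist and client, the residual intraclass (controlling for pretreatment ratings) correlation will be calculated". For the last model: "in Model 3 a random slope for feedback will be added to examine if the effect of feedback varies across therapists". The section *Alliance and outcome* also uses patient and therapist levels.

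**What the care looks like.** Under *TAU condition: treatment as usual*, which describes the care given in both arms, "treatment is delivered as much as possible by the same two therapists". The same section says that caseloads are partly shared, that staff work in co-therapy, and that the group of residents turns over every six months. Under *Patients in crisis*: "changes in staffing are sometimes inevitable and the standard approach is to work with co-therapy pairings". The article draws one consequence there: "So the therapeutic relationship is split up between several people, which might complicate the feedback about the alliance". The *Conclusion* repeats this as a limit on interpreting alliance. Neither section carries it over to the multilevel models.

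**The concern.** Strict nesting means that each patient belongs to exactly one therapist. The article describes two or more therapists per patient as the normal arrangement, so the stated structure is wrong as written. This is not a detail left to an analysis plan, because the article asserts the structure and gives it as the reason for the model.

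To fit the nested model, someone must assign each co-treated patient to one therapist. The other therapist's contribution then goes into the residual, or is absorbed into the first therapist's effect if the two always work together. In either case the therapist variance no longer means what the section on therapist variation says it means.

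The article argues under *Design benefits and drawbacks* that differences between therapists exceed differences between methods, and it plans separate papers on these analyses. An attenuated slope variance could be read as feedback working equally well for every therapist, and an attenuated intraclass correlation as therapists mattering little.

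**Working it through.** **The plan's own figure.** The article gives no therapist variance, intraclass correlation or slope variance to reproduce. Its one design figure is 80% power with 90 per group, one-tailed alpha 0.05, means 1.0 and 1.3, and SD 0.80. This reproduces at 80.8% and does not involve therapists.

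**Inputs.** From the article: two therapists per patient as far as possible, all therapists in both arms, 180 patients, and 6 + 10 + 2 + 1 = 19 permanent staff plus an unstated number of residents. Assumed, because the article is silent: the share w carried by the therapist to whom the patient is assigned, the pairing pattern, and whether co-therapists' effects average or add.

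**Step 1: averaging.** Let therapist effects u be independent with variance σ². A patient's therapist contribution is w·u₁ + (1−w)·u₂, and the model knows only therapist 1. The nested model's therapist variance is the covariance between two patients assigned to the same therapist.

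- Random pairs: the patients share u₁ only, so the covariance is w²σ².
- Fixed pairs: they share both, so the covariance is [w² + (1−w)²]σ².

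The same algebra applies to the random slope for feedback.

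| w | Random pairs: w² | Fixed pairs: w² + (1−w)² |
|---|---|---|
| 0.5 | 0.25 | 0.25 + 0.25 = 0.50 |
| 0.7 | 0.49 | 0.49 + 0.09 = 0.58 |
| 0.8 | 0.64 | 0.64 + 0.04 = 0.68 |
| 0.9 | 0.81 | 0.81 + 0.01 = 0.82 |
| 1.0 | 1.00 | 1.00 |

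For illustration, an assumed true therapist variance of 0.10 would be estimated at about 0.025 to 0.050 for w = 0.5, and at 0.081 to 0.082 for w = 0.9.

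**Step 2: adding.** If the contribution is u₁ + u₂, patients in the same fixed pair have covariance 2σ². The nested model then reports twice the single-therapist variance, so the direction of the error reverses.

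**Step 3: simulation at trial size.** The averaging case was simulated with 180 patients, 20 therapists and 1,000 runs per case. The assumed therapist variance was 0.08 and the assumed slope variance 0.15.

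- Equal shares, random pairs: 24% of the therapist variance and 21% of the slope variance recovered.
- Equal shares, fixed pairs: 42% and 46%.
- w = 0.9: about 75% to 80% in all cases.

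The Monte Carlo standard error of the slope ratio was about 0.04, so these agree reasonably with the formulas.

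**Step 4: the treatment comparison.** In the same simulations the true feedback effect was 0. Its mean estimate lay between −0.010 and 0.006 in every case, so the average effect is not biased.

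**The case against.** The strongest reply is that the size is unknown and the analyses affected are not the main ones. Most of this stands.

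- **Size.** A reader might infer that therapist variance will be badly underestimated, for example that a true 10% share would appear as 2% to 5%. That is only the equal-share case. The article gives no session shares or pairing pattern. Under averaging the loss runs from 0 to 75%, and under adding with fixed pairs the error goes the other way.
- **Low precision in any case.** For a one-way F test at 0.05 with 180 patients in 20 to 40 equal groups (an assumed range), power to detect a true share of 10% is only 50% to 67% with perfectly nested data. At 5% it is 22% to 34%, and at 2.5% it is 12% to 16%. Attenuation makes a missed effect more likely, but the correct model could also miss one.
- **Client effects.** A reader might also infer from the plan for Model 1 ("the presence of therapist and client effects will be tested by controlling for pretreatment functioning at Level 1") that client variance cannot be separated from residual error. The article does not support this. It does not say that only one score per client enters the model, it schedules repeated measurements, and it refers the model's form to a cited analysis that is not available here.
- **Residents.** Their turnover alone does not break nesting. It adds therapists, and it matters only for patients whose treatment spans a changeover.
- **Place in the plan.** The multilevel model in the primary section is additional to the repeated-measures analysis, and Models 1 to 3 are secondary.

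What the reply does not remove is the contradiction: the article asserts one therapist per patient in the analysis and two in the description of care.

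**Conclusion.** The point holds in a limited form. The stated nesting contradicts the described co-therapy, and a single-therapist model would misestimate the therapist variance and the random-slope variance. If co-therapists' effects average, the share recovered is 25% to 50% at equal contributions, 49% to 58% at w = 0.7, 81% to 82% at w = 0.9 and 100% at w = 1. Attenuation is therefore the likelier error, but neither its size nor, strictly, its direction can be settled from the article.

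A reader might go further and doubt the feedback comparison itself. The documents do not support that: therapists work in both arms, and the average effect was unbiased in every scenario simulated. The consequence is confined to the therapist-variation, random-slope and related alliance models, where a weak or absent therapist effect could be reported wrongly. It is worth correcting, but it does not threaten the trial's main comparison.

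**What to change.** Replace the nesting statement in *Primary analysis: EXP versus TAU*, and the models in *Feedback and client and therapist variation* and *Alliance and outcome*, with one of two options:

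1. A multiple-membership model in which each patient's therapists are weighted by their share of that patient's sessions. Use equal weights where co-therapists attend jointly or session records are lacking.
2. A rule, set before analysis, that names one primary therapist per patient, with the multiple-membership model reported as a sensitivity analysis.

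Under either option, report the distribution of therapists per patient and of session shares, so that readers can judge the likely attenuation. State two limits: individual therapists cannot be separated within pairs that always work together, and precision for therapist variance and slope is low with 180 patients.

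The cost is extra analysis work and extraction of the treating therapists from the clinical record. The article does not say whether therapist per session is recorded, which is why the equal-weight fallback is needed. No additional patients or questionnaires are required.

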#### Secondary analyses

The following secondary analyses will be presented in separate papers following the paper on the primary outcomes.

### Feedback and client and therapist variation

If some therapists are generally more effective than others, then the outcomes of clients seen by the same therapists will be correlated. Three multilevel models will be constructed to examine therapist and client effects as well as the effects of feedback on posttreatment functioning, similar to the analysis by Anker et al. [31]. In Model 1, the presence of therapist and client effects will be tested by controlling for pretreatment functioning at Level 1 and evaluating the residual intraclass correlations. To determine the variance due to therapist and client, the residual intraclass (controlling for pretreatment ratings) correlation will be calculated. In Model 2, the effect of feedback will be estimated, and in Model 3 a random slope for feedback will be added to examine if the effect of feedback varies across therapists.

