### Feedback instruments

The feedback studies that meet the requirements that can be derived from the findings of Knaup as mentioned above, are the studies using the Outcome Questionnaire 45 (OQ45) of Lambert and the Partners for Change Outcome Management System (PCOMS) of Miller and Duncan [26,27]).

In the most recent meta-analysis, Lambert & Shimokawa [28] performed a meta-analysis of the effects of both the OQ45 and PCOMS, including a total of 9 randomized controlled trials. This study comprises six randomized studies on the OQ45 and three randomized studies on PCOMS. The latter concerning individual therapy in a student counselling university setting [29], and couples therapy in the context of an (American) university therapy training programme [30], respectively a (Norwegian) family counselling agency [31].

Lambert & Shimokawa found effects sizes varying from .23 to .33. They concluded that the number of psychotherapy patients who deteriorate (5–10% in adult therapy, 14–24% in child psychotherapy, in routine care) can be cut in half by use of these systems. Here also, the main effect comes from identifying Not On Track clients in good time. However, in some of the studies analyzed also beneficial effects were reported for ‘On Track’ clients [31-33].

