#### Procedures and time points

Initial assessment (the 'baseline measurement') takes place when patients first come into contact with the Crisis Intervention & Brief Therapy Team. The intervention lasts a maximum of six months and stops when treatment ends or after six months.

The PCOMS questionnaires are completed and discussed at every session in the EXP condition. In the TAU condition, every six weeks the ORS form is completed and handed over to a research assistant, without discussing it with the therapist. In both conditions, starting at the time of the baseline measurement, additional questionnaires (BSI, HAQII) are completed by patients in both conditions after 6 weeks, 12 weeks, 18 weeks and 24 weeks of treatment. The therapist also completes questionnaires at the same point in time (6, 12, 18 and 24 weeks after treatment starts) about the course of treatment (CGI) and the alliance (HAQII). When treatment ends, all questionnaires are being completed once again. The follow-up measurement takes place three months after the end of treatment.

Before the study starts, the therapists are required to complete a one-off questionnaire measuring their attitude to the instrument and their motivation with respect to the use of feedback in general. The same questionnaire will be completed by the therapists after the study period.

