### Alliance and outcome

The relationship between early change, the alliance, and outcome will be examined at posttreatment and follow-up. These relationships will be analyzed in a similar manner as described in Anker et al. [33], using multilevel analysis in which the levels of patient and therapist will be taken into account. Pretreatment scores and early change will be included as covariates. Patterns in alliance scores of clients ad therapists will be examined to determine whether different patterns of alliance development differentiate outcomes, comparing clusters using chi-square analysis (clinical significant change used as cut off score) as well as ancova analysis (outcome added as a continuous measure).

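### Model 1 promises a client variance and a test of client effects, but with one posttreatment score per patient client variance cannot be separated from error

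*Protocol article*

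**What the plan says.** All of this is in the protocol article.

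- **Feedback and client and therapist variation** (secondary analyses) sets the outcome: "Three multilevel models will be constructed to examine therapist and client effects as well as the effects of feedback on posttreatment functioning". For Model 1 it says that "the presence of therapist and client effects will be tested by controlling for pretreatment functioning at Level 1 and evaluating the residual intraclass correlations". It continues: "To determine the variance due to therapist and client, the residual intraclass (controlling for pretreatment ratings) correlation will be calculated". Model 2 then estimates the feedback effect, and Model 3 lets that effect vary across therapists. The section describes the approach as similar to a cited analysis (reference 31).
- **Primary analysis: EXP versus TAU** gives the nesting: "Since in this design patients are nested within therapists, these nested data will also be examined in a multilevel analysis, controlling for therapist variation".
- **Alliance and outcome**, the companion secondary analysis, names the same two levels: "using multilevel analysis in which the levels of patient and therapist will be taken into account". It treats the end of treatment and the follow-up as separate occasions: "The relationship between early change, the alliance, and outcome will be examined at posttreatment and follow-up".
- **Procedures and time points** gives one end-of-treatment score per instrument: "When treatment ends, all questionnaires are being completed once again". It also lists completions at 6, 12, 18 and 24 weeks and a follow-up three months after treatment. Model 1 does not mention using these.

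**The concern.** Model 1 promises two results about clients: a test of whether client effects are present, and the variance due to clients. To separate a client effect from error, there must be more than one observation per client, or some other level below the client. A patient has one pretreatment score per instrument. Entering that score at Level 1 therefore makes the patient the lowest level, and the Level 1 residual contains both the stable difference between clients and everything else: measurement error, transient fluctuation and unexplained change.

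At stake is what the secondary paper can conclude. If the Level 1 variance is reported as a client effect, error is presented as a property of clients. The promised test would have no parameter to test.

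**Working it through.** **The plan's own figure.** The article gives no number for Model 1. Its only design figure is the power in the sample size calculation: 90 per group, means 1.0 and 1.3, SD 0.80, one-tailed alpha 0.05. This gives 0.3 / (0.80 × √(2/90)) = 2.516 and 2.516 − 1.645 = 0.871, so power is 0.808. The stated 80% is reproduced. The point here does not depend on it.

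**Model as read.** For patient i of therapist j, with one posttreatment score:

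y_ij = b0 + b1·pre_ij + u_j + c_ij + e_ij, with variances σ²_T (therapist), σ²_C (client) and σ²_e (error).

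**What the data can show, given the pretreatment score:**

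- variance of one score: σ²_T + σ²_C + σ²_e
- covariance of two patients of the same therapist: σ²_T
- covariance of patients of different therapists: 0

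Two non-zero quantities are observed for three unknowns. σ²_T is identified. σ²_C and σ²_e appear only as a sum. The residual intraclass correlation is σ²_T / (σ²_T + σ²_C + σ²_e), and one minus it is the share of client plus error.

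**With two or more scores per patient,** a further quantity appears: the covariance of two scores of the same patient, σ²_T + σ²_C. All three variances are then identified.

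**Numerical check.** Inputs:

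- 180 patients (2 × 90, from the sample size calculation).
- 19 therapists. This is an assumption: the permanent staff listed under Patients in crisis number 6 + 10 + 2 + 1 = 19, and the number of rotating doctors is not given.
- Total variance 0.80² = 0.64.
- Therapist intraclass correlation 0.05 (an assumption), so σ²_T = 0.05 × 0.64 = 0.032 and client plus error = 0.608.
- Simulated client variance 0.60 × 0.64 = 0.384, which is 0.384 / 0.608 = 0.63 of the within-therapist variance.

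The covariance is V = σ²_T·A + σ²_C·C + σ²_e·I, where A marks pairs of scores with the same therapist, C marks pairs from the same patient, and I is the identity matrix.

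| Scores per patient | Rank of {A, C, I} | Log-likelihood by client share of within-therapist variance |
|---|---|---|
| 1 | 2 | -199.113030 at 0, 0.25, 0.5, 0.63, 0.75 and 0.99 |
| 2 | 3 | -437.66 at 0; -413.71 at 0.25; -397.19 at 0.5; -394.62 at 0.63; -405.86 at 0.75; -3571.86 at 0.99 |

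With one score per patient, C equals I, so the likelihood is flat in the client share. With two scores it is highest, among the shares tried, at the simulated share of 0.63.

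**Range over the assumptions.** C equals I whatever the number of therapists and whatever the intraclass correlation, so the flat result does not depend on either. The intraclass correlation only changes the size of the undivided remainder: 0.99 at 0.01, 0.95 at 0.05, 0.90 at 0.10.

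**The case against.** **One score per patient is inferred.** The section does not state the number of scores, the instrument or the number of levels, and a condensed article may leave these to a fuller document. This stands as a limit on certainty. But the outcome is posttreatment functioning, the pretreatment score is placed at Level 1, and the neighbouring sections name only patients and therapists. If occasions were meant to be Level 1, the pretreatment score would be constant within a patient and would belong one level up. Either reading needs a correction to the text.

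**Client variance may simply mean the Level 1 residual.** In a two-level model the within-therapist part is often loosely called client variance, and the second sentence on Model 1 speaks of a single intraclass correlation, which yields exactly that split. This largely stands: on this reading the variance statement is a labelling fault. It does not rescue the test. A Level 1 residual variance of zero is not a meaningful null hypothesis, so nothing corresponds to testing whether client effects are present.

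**Stronger readings that the documents do not support:**

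- A reader might infer that the software will fail to converge, or that any client share between zero and the whole remainder could be reported. That would require a patient random intercept on top of the residual, and the article specifies none. The ordinary two-level model has no such term.
- A reader might infer that a middle level was carried over from the cited couples study. The article says only that the study concerned couples and that the analysis will be similar. The levels of that study are not described, so this explanation would be an assumption, and the argument does not need it.
- A reader might infer that the feedback results are undermined. Models 2 and 3 estimate the feedback effect and its variation across therapists, and neither needs client variance separated from error.

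**Therapists work in pairs.** The article describes co-therapy, so a patient may not belong to one therapist. That affects how the therapist term is built. It does not change the present point, because with one score per patient the client and error terms still coincide.

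**Conclusion.** The point holds in a limited form. If Model 1 uses one posttreatment score per patient, with patients nested within therapists, it identifies the therapist variance and the sum of client variance and error, and nothing finer. The stated test of client effects does not exist under that model, and the stated client variance can only be client plus error.

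The therapist intraclass correlation, the feedback effect, the random slope and the primary EXP versus TAU comparison are untouched by this point. It is a minor, wording-level correction to one secondary analysis, and it changes only what the resulting paper may say about clients. The conclusion rests on the inferred single score per patient, and not on the assumed number of therapists or the assumed intraclass correlation.

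**What to change.** **Main change.** State that Model 1 has two levels, patients within therapists. Report and test only the therapist intraclass correlation, label the Level 1 variance as client plus error, and delete the test of client effects. Models 2 and 3 can stay as they are.

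**If a client variance is wanted.** Specify an additional three-level model, with occasions within patients within therapists, on the repeated scores already collected, and enter the pretreatment score at the patient level. Name the instrument and the occasions used. State that this model addresses functioning over time and not posttreatment functioning alone, so that it supplements Model 1 and does not replace it.

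**Cost.** The main change is wording only. The optional model adds an analysis but needs no new data.
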